## Materials and Equipment

Exclusion criteria for participants will be as follows: (1) less than 7 years and more than 9 years old; (2) use of psychoactive drugs; (3) absent from interventions (in which cases data from this participant will be excluded from analysis, but they will continue to participate in the intervention) and (4) diagnose of sleep disturbance or any health problems, such as neurological disorders, and psychiatric, cardiovascular or genetic diseases. Thus, to characterize the sample and to verify inclusion criteria questionnaires and scales will be applied, and strategies developed by researchers with parents/guardians and their children. These measures and the serious game itself are described below.

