#### Sleep Disturbance Scale for Children

This scale was elaborated by Bruni et al. (1996) and validated to use in Brazil. It is composed by 26 items, with a self-report rating that assesses sleep disorders in children, answered by parents. The scale has six factors: (1) disorders of initiating and maintaining sleep; (2) sleep breathing disorders; (3) disorders of disturbance and nightmares; (4) sleep wake transition disorders; (5) disorders of excessive somnolence; and (6) sleep hyperhidrosis. Each item is assessed on a five-point scale from “never” to “always” and higher scores indicate more sleep problems (Bruni et al., 1996; Nascimento-Ferreira et al., 2016).

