Upon enrolment, the four stages of research will be followed, counting on the participation of children and their parents/guardians. All encounters with parents/guardians will happen at 6:40 pm, after the children’s classes, due to the parent’s convenience. First, during the stage of pre-intervention, questionnaires and scales will be applied to assess sociodemographic data, and characterize sleep habits and sleep pattern, by filling out the UNESP sleep habits and hygiene scale (child version) and sleep diary, besides giving the actiwatch to be wore by the children. Parents will also answer the Sleep Disturbance Scale for Children to identify the presence of sleep disorders. After this, parents from experimental group will participate in a workshop conducted by the research team about sleep habits and the importance of healthy sleep in childhood. The team will be available for an additional encounter 1 week after evaluation to clarify doubts about filling in the sleep diary and/or use of actiwatch.

The children themselves will be active in the evaluation steps. All evaluations with them will occur on the first Monday after each meeting with parents, once research begins with the parent’s authorization. In this stage, the children will answer the Pictorial Sleepiness Scale of Maldonado to evaluate sleepiness levels and will characterize their bedroom and the activities that they do before sleep at night, using, respectively, the strategies “Set up your bedroom” and “Mapping activities before bedtime.”

After pre-intervention evaluation, the experimental group will be submitted to the intervention with our serious game “Perfect Bedroom: learn to sleep well,” which will be conducted by three researchers during the children’s classes, at 02:00 pm on Tuesdays and Thursdays (see section “Intervention”).

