### Intergroup and Intragroups Analysis

Once confirmed that the groups did not present significative differences, the comparison procedure will be conducted. Variables included in sleep patterns (sleep latency, sleep efficiency, sleep and waking up times, total sleep time), sleep hygiene and sleep problems will be considered dependent variables and will be compared between experimental and control groups, during the three points in time where they will be evaluated, using independent student’s *t*-test and chi-square (χ^2^) with odds ratio and dimension of association (Phi and Cramer’s V), depending on the nature of the data. It will allow us to identify if the intervention with the serious game yielded improvements in objective sleep measures and sleep hygiene.

To evaluate possible improvements intragroup, comparisons will be conducted using: ANOVA (F) for repeated measures with Bonferroni’s post test and Q Chochran test. For all numeric variables percentage will be calculated with delta differences (post-test score minus the pre-test score) and percentage’s change [(post-test score) minus (pre-test score) divided by (pre-test score) multiplied by 100]. These measures will allow us to evaluate the intervention’s immediate effects and the maintenance of this effect after 4 weeks.

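### If the Sleep Disturbance Scale for Children both screens children out and supplies the sleep-problems outcome, the within-group tests of that outcome lean towards apparent worsening in both arms

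*Protocol article*

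**What the plan says.** Materials and Equipment lists as an exclusion "4) diagnose of sleep disturbance or any health problems, such as neurological disorders, and psychiatric, cardiovascular or genetic diseases". It names no instrument and no cut-off, and goes on to say that "to characterize the sample and to verify inclusion criteria questionnaires and scales will be applied".

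Under Measures, the SDSC is the instrument that "assesses sleep disorders in children, answered by parents". It has 26 five-point items, and a higher score means more sleep problems. The Sociodemographic and Health Questionnaire separately asks parents about present or past sleep disorders.

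Design and Procedures places the SDSC at the pre-intervention stage: "Parents will also answer the Sleep Disturbance Scale for Children to identify the presence of sleep disorders". For the two later assessments it says that parents re-rate sleep habits and patterns, and does not name the SDSC.

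Intergroup and Intragroups Analysis states that "sleep hygiene and sleep problems will be considered dependent variables and will be compared between experimental and control groups" at the three time points. It adds: "To evaluate possible improvements intragroup, comparisons will be conducted using: ANOVA (F) for repeated measures", with Cochran's Q, differences from pre-test and percentage change. It reads these measures as showing the short-term effect of the intervention and whether that effect lasts.

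**The concern.** The condition excluded at entry and the condition the SDSC is given to detect are the same. The wording used for a high SDSC score is also the wording used for the outcome. If the SDSC result decides exclusion (4), children enter only when their baseline value of an outcome is low. Some of them scored low partly by chance, so the group mean rises at the next measurement with no real change (regression to the mean).

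The drift runs against the hypothesised benefit. A within-group test would tend to hide a real improvement or suggest a deterioration, and the analysis section reads such change as an effect without any caution. What is at stake is the interpretation of one outcome. The Abstract names sleep habits as primary and sleep parameters as secondary.

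**Working it through.** **Inputs from the article.** 88 children per arm (Participants); three assessments (Design and Procedures); 5% level (Proposed Analysis); repeated-measures ANOVA and Cochran's Q within groups, t-test and chi-square between groups (Intergroup and Intragroups Analysis).

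The 88 reproduces as a one-sided t-test at d = 0.5 and 95% power (87.3, rounded up to 88). Two-sided gives 105. That is a separate matter and is used here only as the group size.

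**Assumptions not in the article.** Share screened out on the SDSC, q = 5% to 30%; test-retest correlation r = 0.5 to 0.9; normal scores; the same screening rule in both arms; children independent of each other.

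**Expected drift.** Let c be the standard normal cut-off with a share q above it, and φ the normal density. Children below c have mean baseline score −φ(c)/(1−q) in SD units. With no true change, their later mean is r times that. The apparent rise is therefore

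(1−r) × φ(c)/(1−q).

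- q = 5%: c = 1.645, φ = 0.103, φ/(1−q) = 0.109; rise 0.011 (r = 0.9) to 0.054 (r = 0.5)
- q = 10%: c = 1.282, φ = 0.175, φ/(1−q) = 0.195; rise 0.019 to 0.097
- q = 20%: c = 0.842, φ = 0.280, φ/(1−q) = 0.350; rise 0.035 to 0.175
- q = 30%: c = 0.524, φ = 0.348, φ/(1−q) = 0.497; rise 0.050 to 0.248

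**False-positive rates.** 1,500 simulated trials per setting, with no true change and no treatment effect. Each score is a stable part with variance r plus independent error with variance 1−r. Only children below c at baseline are enrolled. Ranges run over r = 0.9 to 0.5.

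| Screened out | Within-group ANOVA, numeric score | Cochran's Q, split at the screening cut-off |
|---|---|---|
| 0% | 4.4-5.4% | not applicable |
| 5% | 5.3-9.4% | 13-37% |
| 10% | 6.7-15.1% | 35-86% |
| 20% | 9.5-40.7% | 77-100% |
| 30% | 17.1-72.4% | 95-100% |

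The Monte Carlo standard error at a true 5% is √(0.05 × 0.95/1500) = 0.56 percentage points, so the 0% row is nominal.

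**If the outcome is split at the screening cut-off.** Baseline is 0 of 88 against 0 of 88, so the baseline odds ratio is undefined. At a later visit 1.9% to 20.6% of children count as cases, which is 0.019 × 88 = 1.7 to 0.206 × 88 = 18.1 children per arm, with no real change.

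**Between arms.** At a post-baseline visit the unadjusted t-test rejects in 4.1-6.1% of null trials and the chi-square in 3.6-5.7%. The selection acts alike in both arms and cancels. The simulation treats children as independent, so it says nothing about the effect of allocating by class.

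**The case against.** The strongest reply is that the double use of the SDSC is inferred. Exclusion (4) speaks of a diagnosis, and the health questionnaire could supply it. Design and Procedures has the SDSC detect disorders but never says a child is removed on its score. The outcome link is inferred too: the analysis section names no instrument for sleep problems, the UNESP scale also has items on bedtime resistance and daytime somnolence, and the SDSC is not named at re-assessment. All of this stands, and it makes the point conditional. The inference is still the natural one. The SDSC is the only listed scale said to assess sleep disorders, and it is the only one whose score is described in terms of sleep problems.

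A reader might go further and infer that every child starts free of sleep problems, so that the within-group tests are bound to show worsening. The article does not support this. The SDSC is a graded score that is nowhere dichotomised, so children below a cut-off still differ and can improve. The empty baseline and the high Cochran's Q rates both need a split at the screening cut-off.

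It is also true that the comparison free of this bias is already planned, since the arms are compared at each time point, and that the primary outcome has its own scale. What remains is that the article also reads the within-group results as effects.

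**Conclusion.** The point holds conditionally and for one outcome. If the SDSC result feeds exclusion (4) and the SDSC supplies sleep problems, the within-group tests, differences and percentage changes for that outcome are biased towards apparent worsening in both arms.

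For the numeric score the bias is small when 5-10% are screened out: about 0.01-0.1 SD, with ANOVA false positives about 5-15%. With 20-30% screened out, false positives are about 10-72%. It is severe only under dichotomisation at the screening cut-off, with Cochran's Q at 13-100%. These sizes rest on the assumed screening share and test-retest correlation, which the article does not give. If only a prior reported diagnosis excludes a child, the distortion is smaller.

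The between-arm comparison and the primary outcome are not biased by this mechanism. A claim that the trial would therefore miss a real benefit or report harm goes beyond the evidence, because the control arm would show the same drift.

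**What to change.** 1. In Intergroup and Intragroups Analysis, state that within-group change in sleep problems (ANOVA, Cochran's Q, difference and percentage change) will not be interpreted as an intervention effect.
2. Base inference for this outcome on the between-arm difference in SDSC score at post-intervention and at follow-up, adjusted for the baseline SDSC score. The adjustment is for precision; the comparison is free of this bias without it.
3. Reconcile Materials and Equipment, the Sociodemographic and Health Questionnaire and Design and Procedures on whether exclusion (4) rests on a reported diagnosis or on the SDSC result. Also name the SDSC among the later assessments if it is the source of this outcome.

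The cost is a change of wording and the loss of the within-group result for this one outcome. The baseline score is already collected, and the analysis section already implies the later ones.

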### Measures

#### Sociodemographic and Health Questionnaire

This questionnaire was designed to collect information about health, daily activities and demographic characteristics from parents and their children. It will be responded by parents and contains questions on:

(1) Child data: birth date; age; gender; grade level; potential sleep disorders, present or past; child’s medical and psychological condition; use of any medication or treatments; and additional activities of children.(2) Family data: job and education level of both parents, marital status, number of family members living with child and number of brothers/sisters.

#### Socioeconomic Status Questionnaire

The questionnaire allows inference of the family income and stratifies the population into six economic classes (A, B1, B2, C1, C2, D-E). This criteria was established by the Brazilian Association of Research Companies (Associação Brasileira de Empresas de Pesquisa – ABEP) and considers: possession of comfort/high value objects (washing machine, car, freezer, etc.), access to public services (e.g., potable water) and the level of education of the family member who contributes most to family income (Associação Brasileira de Empresas de Pesquisa [ABEP], 2014).

#### UNESP Sleep Habits and Hygiene Scale (Child Version)

This scale contain 16 questions and will be used to evaluate characteristics of children’s sleep, according to four indicators that are considered causal to sleep hygiene: sleep routine (activities realized before bedtime); physiological alert (diurnal habits that would promote excitement or physical discomfort near to bedtime); cognitive/emotional aspects (indicators of emotional regulation and wellbeing before bedtime) and sleep environment (adequate sleeping environment in terms of temperature, comfort, and organization) (Pires et al., 2012). Each item is assessed on a five point of frequency scale from “never – no day” to “always – every day.” Furthermore, the scale contains five questions to evaluate bedtime resistance and daytime somnolence, assessed also on a five-point scale of frequency. Higher scores indicate worst habits of sleep hygiene. This has been empirically validated for use in Brazil.

#### Sleep Disturbance Scale for Children

This scale was elaborated by Bruni et al. (1996) and validated to use in Brazil. It is composed by 26 items, with a self-report rating that assesses sleep disorders in children, answered by parents. The scale has six factors: (1) disorders of initiating and maintaining sleep; (2) sleep breathing disorders; (3) disorders of disturbance and nightmares; (4) sleep wake transition disorders; (5) disorders of excessive somnolence; and (6) sleep hyperhidrosis. Each item is assessed on a five-point scale from “never” to “always” and higher scores indicate more sleep problems (Bruni et al., 1996; Nascimento-Ferreira et al., 2016).

#### Sleep Diaries

Sleep diaries are an extremely helpful tool to assess sleep patterns (Carney et al., 2012). We adapted a model of a diary and each page contains questions about children’s sleep for each day, forming a booklet that will be answered by the parents over 10 days. It will provide information about: (1) sleep and wake-up times, (2) sleep latency (amount of time taken from bedtime until the child falls asleep), (3) number of awakenings during the night, (4) total sleep time, and (5) naps timing and duration. Additionally, it was included questions on: activities before bedtime, how the child woke up and why; and parent’s perception of wellbeing of their child after each night of sleep. These measures will be registered over the 10 nights, allowing the researchers to examine the children’s habitual sleep patterns in weekdays and weekend.

#### Actigraphy

Actigraphy will be used to objectively measure sleep/wake behavior, using the Actiwatch model AT5030 (Condor Instrument, São Paulo, Brazil). This device measures activity, temperature and exposure to light. Taken together, these measures and the information from sleep diaries can be used to properly assess sleep and wake patterns of children. Actiwatches will be used by children on their non-dominant wrist over 10 days and while parents will be responding sleep diaries. Child and parents will be informed about the guidelines for actiwatch use, including always using the actiwatch, except when engaging in contact sport, bathing, or swimming, and to not apply perfume or moisturizer near the device. Further, the use of the event marker will be encouraged to indicate bedtime and wake time. Additional information was included in the sleep diaries to reinforce how to use the device. The following variables will be derived from the actigraphy records: (a) total sleep time (the total of sleep obtained during a sleep period); (b) sleep latency (amount of time taken from bedtime until the child falls asleep), and (c) sleep efficiency (i.e., number of hours slept/number of hours spent in bed × 100) (Markovich et al., 2015).

#### Strategy “Set Up Your Bedroom”

This strategy was created by the researchers to characterize a child’s bedroom according to their perception. Each child will receive one kit with one sheet of paper A4 to set up your bedroom and 17 stickers that represent common objects that could be in bedrooms, such as: bed, wardrobe, pillows, lamps, video game, cell phone, television, etc. (**Figure 1A**). After that, they will read and apply the following instruction: “I would like you to select the stickers that represent objects presents in your bedroom currently. Do not paste stickers of objects that you would like to have or have had. If the stickers lack any object, you can draw it.” In addition, this strategy will be used to measure what the child knows or is able to do as a result of playing the serious game “Perfect Bedroom: learn to sleep well” (Calderón and Ruiz, 2015).

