#### Strategy for Mapping Activities Before Bedtime

This strategy was also developed by researchers and assesses the activities that the child usually does at night and before sleep. Each child will receive one kit with one sheet of paper A3 and fifteen stickers that represent common activities that they could do before sleep at night, such as: take a bath, play video games, brush their teeth, watch TV, read, listen to music, do homework, turn off the lights (**Figure 1B**). After that, they will read and apply the following instruction: “I would like you to select the stickers that represent activities that you do at night and before sleep. Do not paste stickers of activities that you would like to do. If the stickers lack any activity you can draw it.” Similarly to the strategy described above, this one will be used to measure the knowledge the children have and what they are able to do as consequence of playing serious game (Calderón and Ruiz, 2015).

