#### Evaluation of Serious Game “Perfect Bedroom: Learn to Sleep Well” by Children

For the purpose of allowing the children to evaluate the serious game, we developed a questionnaire with textual and graphics elements. It includes quality characteristics that current literature indicate to be relevant to evaluate serious games (Calderón and Ruiz, 2015) and contains questions on:

(1) User’s satisfaction and user’s experience, to evaluate their attitude and behavior related to the game.(2) Understandability, to assess the ability of the serious game of being understood.(3) Enjoyment, to assess if the game provides a fun experience to the users.(4) Learning outcomes, to identify what the users will be able to do as a result of playing this serious game. These measures will be provided from comparisons between the results from pre and post-intervention of the strategies “Set up your bedroom” and “Mapping activities before bedtime.”

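### The two sticker tasks record the child's current bedroom and routine, so they cannot support the conclusion about the child's knowledge that the protocol draws from them

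*Protocol article*

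**What the plan says.** The section on the *Set Up Your Bedroom* strategy gives the child's instruction word for word: "I would like you to select the stickers that represent objects presents in your bedroom currently", followed by "Do not paste stickers of objects that you would like to have or have had". The task's first stated purpose is to describe the room as the child sees it. A second purpose is then added: "this strategy will be used to measure what the child knows or is able to do" as a result of the game.

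The section on mapping activities before bedtime has the same structure. The child is told "I would like you to select the stickers that represent activities that you do at night and before sleep" and "Do not paste stickers of activities that you would like to do". The section then states that "this one will be used to measure the knowledge the children have and what they are able to do" as a consequence of playing.

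The section on the children's evaluation of the game lists, as its fourth element, "Learning outcomes, to identify what the users will be able to do as a result of playing this serious game". It obtains this element by comparing the two sticker tasks before and after the intervention. The analysis section on evaluating the game confirms this: learning outcomes come from between-group and within-group analysis of the two tasks. Each bedroom object is coded absent or present, and unsuitable and suitable objects are counted. Activities are handled in the same way.

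**The concern.** The instruction and the stated use do not match. A child who follows the instruction has no means of showing what a good room or routine would be, because anything not already there or already done must be left off. The result is nevertheless to be read as knowledge.

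The error can run both ways. Knowledge gained but not yet acted on at home leaves the sheet unchanged. A change made by parents alters the sheet even if the child has learned nothing.

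This bears on the trial's own rationale. The Introduction faults an earlier programme for not assessing the children's knowledge and describes that assessment as largely missing from previous interventions. As instructed, these tasks do not fill that gap. A later analysis plan cannot repair this, since the wording given to the child is already fixed.

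**Working it through.** No figure in the protocol bears on this point, so the check is a comparison of the sections.

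**1. What is elicited against what is claimed**

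| Task | Child is asked for | Child must leave out | Claimed to measure |
|---|---|---|---|
| Bedroom (17 stickers) | objects there now | objects wished for or formerly owned | what the child knows or can do |
| Activities (15 stickers) | activities actually done | activities wished for | knowledge, and what the child can do |

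Both claims have two parts, knowledge and ability. The instruction fits enacted behaviour, which is one reading of ability. It does not fit knowledge.

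**2. What a single item can show.** As an illustration, take a child whose room has a television at baseline (television is one of the stickers).

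| Child learns that it is unsuitable | Television afterwards | Item before, then after |
|---|---|---|
| yes | stays | present, present |
| no | stays | present, present |
| yes | removed | present, absent |
| no | removed by parents | present, absent |

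The item follows the second column only. Rows 1 and 2 look identical, and so do rows 3 and 4. Under the instruction as written, the item does not separate a child who learned from one who did not.

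**3. Does the same hold for activities?** Less strongly. A child may decide to read rather than play a video game, so a change can reflect something learned and put into practice. No change, however, still does not show that knowledge is absent.

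**4. Is knowledge measured elsewhere?** The remaining instruments described are:
- the rest of the game questionnaire: satisfaction and experience, understandability, enjoyment, and an open question on what playing was like;
- the UNESP scale, the Sleep Disturbance Scale and the diaries: habits and sleep, completed by parents;
- actigraphy and the pictorial sleepiness scale: sleep and sleepiness.

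None tests what the child knows about sleep hygiene.

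**5. Can a change be credited to the game?** Under *Design and Procedures*, parents in the experimental group attend a workshop on children's sleep. Control parents do not, and control children have no contact with the team beyond evaluations. The between-group contrast in room contents is therefore game plus parent workshop against neither. A change in the room cannot be assigned to the child's learning from the game.

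**The case against.** The best defence is that learning here means behaviour. The Figure 1 caption and the game-evaluation section speak only of what users will be able to do, the Introduction gives behaviour change as an aim of serious games, and the assessment is called ecological. On that reading, asking what the child has and does now is reasonable. This stands for ability, mainly in the activities task. It does not rescue the explicit claims to measure what the child knows (bedroom task) and the knowledge the children have (activities task).

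It is also fair to say that the workshop affects attribution of every outcome in the trial. It is used here only to show that a changed room is not evidence of the child's own learning.

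Some stronger readings are tempting but are not supported:
- *A child who keeps a television scores as having learned nothing.* The scores are counts over 17 and 15 stickers, so other items can still change. The argument holds item by item, not for the whole score.
- *The protocol itself concedes that the sheets reflect household means.* The passage in *Anticipated Results* concerns low-income families and a quiet, dark, comfortable room. It does not say this of electronic devices, on which the scoring is based, or of activities.
- *The tasks are invalid.* They remain usable as child-reported descriptions, which is their first stated purpose.

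**Conclusion.** The point holds for knowledge. As instructed, both tasks measure child-reported bedroom environment and pre-sleep routine, and neither a change nor the lack of one can be read as a change in what the child knows. The case is strongest for the bedroom task and weaker for activities.

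The size of any misreading cannot be derived from the protocol. It would depend on how often knowledge and home circumstances diverge, for which no figure is given. The comparisons affected are those of the learning outcome, on both tasks.

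A reader might infer that the trial's main conclusions are in doubt. They are not. The abstract names sleep habits as primary and sleep parameters as secondary, and these rest on other instruments.

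The conclusion assumes that children follow the instruction as printed, and that no knowledge test exists beyond the instruments described.

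**What to change.** In the two strategy sections, the section on the children's evaluation of the game and the corresponding analysis section, analyse and report both tasks as child-reported bedroom environment and pre-sleep activities. That makes them a direct test of hypothesis (b) in the Introduction. Remove the statements that they measure knowledge, and do not attribute room changes to the child's learning from the game. This is a change of wording only and needs no new data.

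If a knowledge outcome is wanted, add a second sheet in both groups at each evaluation, using the same stickers, that asks for the room and routine best for sleep. Score that sheet as knowledge. Hand it out only after the current-state sheets have been collected, so that it cannot colour them at that visit. The cost is a second set of materials and a few extra minutes per visit. Two drawbacks should be stated: the baseline sheet may cue control children, and the task overlaps with the game's own exercise of assembling a room, so it may partly test recall of the game.
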